### Recruitment

Patients who apply for inpatient therapy via the clinic website (http://www.schoen-kliniken.de/ptp/kkh/bar/anmeldung/krankenhaus/) will be immediately informed about the current trial and can sign up to receive further information. Patients who directly contact the clinic’s head office will receive by mail an information letter that contains the hyperlink to the above-mentioned website.

### Assessment of eligibility and randomisation

After signing up for further information via the website, prospective participants will receive an email from the research team that includes detailed information about the study. They will be asked to send back an informed consent form via e-mail if they are willing to participate. Patients providing informed consent will be interviewed by telephone to clarify whether they fulfill the inclusion criteria. These structured clinical interviews for DSM disorders (SCID) will be conducted by psychotherapists-in-training who will be weekly supervised by an experienced clinician. Participants providing informed consent, meeting all of the inclusion and none of the exclusion criteria will enter the study. They will be randomly allocated to treatment conditions and complete initial assessment. The allocation will be performed by an independent researcher not otherwise involved in the study using an automated, computer-based random integer generator (randlist). The allocation will be concealed in advance from the participants, researchers involved in recruitment, and inpatient therapists. Patients will be informed that they can withdraw from the study at any time, without any consequences for their subsequent treatment. See Figure 1 for participants’ flow throughout the study.

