### Assessments

Self-report and observer-rated assessments will take place at baseline, post-intervention (three weeks after randomisation), at intake for inpatient treatment, weekly during inpatient therapy, and after completion of inpatient therapy (see Figure 1 and Table 1 for a detailed overview). Self-report data will be collected using a secure web-based assessment system (AES, 256-bit encrypted), and observer-based assessments will be conducted via the telephone by trained interviewers. Observer-rated assessments will be recorded to examine interrater reliability. In cases of disagreement, the two raters will discuss until a consensus is formed, and the rating agreed upon will be used for further analyses. If no agreement is reached after discussion, the assessment will be rated by an experienced diagnostic rater, and this rating will be used for analysis.

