### Blinding

The research staff conducting the observer-based rating of depressive symptoms will be blinded to the participants’ assigned conditions. Considerable effort is being undertaken to ensure blindness, including the following: (a) an explanation to the participants as to why it is important not to inform the interviewer about the condition to which they were assigned, (b) a written reminder in the interview manual prompting the interviewer to ask the participant not to inform him or her about the randomisation status, (c) verbal reminders to the patient before the interview, and (d) a documentation after the assessment of whether or not the interviewer is still blind to the treatment condition. If the interviewer finds out about the treatment condition another independent interviewer will conduct the interview instead. Participants will not be blinded to the treatment condition.

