### Primary and secondary outcomes

#### Primary outcome

The primary outcome is depressive symptom severity, as measured by the Hamilton Rating Scale for Depression (HRSD_24_) [51], with assessments conducted pre-and post-treatment. The HRSD is likely the most widely used clinician-rated scale for measuring depression. It assesses depressed mood, vegetative and cognitive symptoms of depression, and anxiety symptoms during the prior seven days. Items are rated on either a five-point or a three-point scale, and the total score is derived by summing the individual item scores. Higher scores indicate greater symptom severity. The HRSD has an interrater-reliability of 0.90 [51] and shows high internal consistency (*α* = 0.88) [52]. Furthermore, it is sensitive to change over time and treatment and corresponds well with overall clinical ratings of severity [53,54]. The cut-off points of 10, 19, 27, and 35 represent the thresholds for mild, moderate, severe, and very severe depression, respectively [52].

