### Statistical analyses

This clinical trial will be conducted in compliance with the protocol of the Declaration of Helsinki and GCP. Aiming at an intention-to-treat design we will include all participants who will be randomly assigned to conditions. Additional per protocol analyses (PPA) will be conducted, including only participants’ satisfying protocol treatment.

Missing data will be handled using multiple imputations (MI). MI is especially robust with respect to missing data [69]. Nevertheless, to assess systematic effects of missing data that cannot be ignored, pattern mixture analyses for multi-level longitudinal approaches [70] will be conducted. To determine whether the treatment effect is dependent on missing data, the missing-data pattern of each participant will first be coded and then included in a three-way interaction (missing-data pattern x condition x change in depression severity) in the main outcome analyses. If no significant interactions between the missing-data pattern and the treatment outcome are found, it can be concluded that it is very unlikely that missing data skewed the results.

The mean improvement scores on all continuous outcome measures will be analysed within and between groups via mixed-model analyses of variance. For all mixed-model analyses, Cohen’s *d*[71] will be calculated by standardising the differences between baseline and follow-up scores by the pooled standard deviation of baseline scores.

The clinically significant improvements between pre-treatment and post-treatment will be examined with regard to the definition of Kroenke (2002) [58]. Differences in response and remission rates will be analysed using chi-square tests. We will also calculate the number needed to be treated (NNT) to achieve response, partial remission, or remission. Time to remission will be measured in days, and the differences between groups in time to remission will be compared using a t-test for independent samples.

Analyses will be performed using an alpha level of 0.05 and one-sided tests will be used for unidirectional and two-sided tests for bidirectional hypotheses. All analyses will be conducted using SPSS 21.

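### The protocol's wording puts random allocation before the baseline assessment and does not say that unblinded patients complete T0 before learning their arm

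*Protocol article*

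**What the plan says.** The section on eligibility and randomisation in the protocol article runs in order of time. After consent comes the SCID: "Patients providing informed consent will be interviewed by telephone to clarify whether they fulfill the inclusion criteria". Those who qualify enter the study, and then: "They will be randomly allocated to treatment conditions and complete initial assessment". On concealment it says: "The allocation will be concealed in advance from the participants, researchers involved in recruitment, and inpatient therapists". The section does not say when patients are told their arm, and it refers to Figure 1 for the participant flow.

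Under Blinding, the raters are covered ("The research staff conducting the observer-based rating of depressive symptoms will be blinded to the participants’ assigned conditions") but the patients are not: "Participants will not be blinded to the treatment condition".

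Table 1 (Study design) lists at T0 the SCID, HRSD, QIDS-C, PHQ-9 and the other questionnaires, including therapy expectations (PATHEV). It describes the column as baseline and as before treatment, not as before randomisation. The primary outcome is the HRSD, "with assessments conducted pre-and post-treatment".

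Under Statistical analyses: "The mean improvement scores on all continuous outcome measures will be analysed within and between groups via mixed-model analyses of variance". Cohen's d is to be formed from baseline-to-follow-up differences divided by the pooled baseline SD. PHQ-9 response is defined as a fall of at least five points.

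**The concern.** A baseline score protects a comparison of change only if the allocation cannot have influenced it. Read as written, the protocol lets the allocation come first. The patients could plausibly react to it: inclusion criterion (e) selects people who are motivated to use the online programme, while the control arm is usual care, which may amount to no treatment. Several T0 measures ask for mood, worry or hope of improvement, which are the answers most open to relief or disappointment.

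A shift at T0 that differs between arms would be counted as part of the difference in improvement. If control patients report worse symptoms at T0 because they are disappointed, and this fades, their improvement is overstated and a real benefit is hidden. A shift the other way would create an apparent benefit. The planned multiple imputation and pattern-mixture analyses deal with missing scores and cannot correct a baseline that was observed but altered.

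**Working it through.** **Order of events.** Setting the relevant texts side by side:

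| Source | What it fixes | What it leaves open |
|---|---|---|
| Eligibility and randomisation | SCID before allocation; allocation named before the initial assessment | When patients are told their arm |
| Concealment sentence, same section | Arm unknown before it is drawn | Whether it is withheld until T0 is complete |
| Assessments: "Self-report and observer-rated assessments will take place at baseline, post-intervention (three weeks after randomisation" | Post-treatment is timed from randomisation | Whether baseline falls before or after randomisation |
| Table 1 | T0 precedes treatment; the SCID is in the T0 column | Whether the other T0 measures precede randomisation |
| Blinding | Raters blinded, patients not | What patients know at T0 |

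No row places the HRSD, QIDS-C or questionnaires before allocation or disclosure. One row, on its plain reading, places them after allocation.

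**The plan's own figure.** Inputs from Sample size: d = 0.40, power 0.80, two-sided alpha 0.05. Equal allocation is assumed, as the ratio is not stated. By the normal approximation, n per arm = 2(1.960 + 0.842)² / 0.40² = 15.70 / 0.16 = 98.1, so 99 per arm and 198 in total. The t-test version gives 99.08, so 100 per arm and 200 in total, with power 0.804. The stated 200 is reproduced and does not depend on the order of baseline and allocation.

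**How a shift carries through.** Let b be the between-arm difference in T0 scores caused by knowing the allocation, with follow-up scores unaffected. Improvement is baseline minus follow-up, so the difference in mean improvement changes by exactly b. With two time points, the group-by-time test in a mixed analysis of variance is the test of that difference.

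**Illustration in HRSD points.** The documents give no HRSD SD; 6 to 8 points is an assumption, and so is a 1-point shift.
- Target effect: 0.40 × 6 = 2.4 points; 0.40 × 8 = 3.2 points.
- Shift in SD units: 1/6 = 0.167; 1/8 = 0.125.
- Shift as a share of the target: 1/2.4 = 42%; 1/3.2 = 31%.

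**Illustration as false-positive rate.** With 100 per arm, an assumed pre-post correlation r, no true effect and b in SD units, the standard error of the difference in change is √(2(1 − r)) × √(2/100). The two-sided rejection rate is 1 − Φ(1.960 − b/SE) + Φ(−1.960 − b/SE). For r = 0.5 and b = 0.10, SE = 1 × 0.1414, b/SE = 0.707, and the rate is 0.109. The full set:

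| b (SD) | r = 0.3 | r = 0.5 | r = 0.7 |
|---|---|---|---|
| 0.05 | 0.060 | 0.064 | 0.074 |
| 0.10 | 0.092 | 0.109 | 0.150 |
| 0.20 | 0.223 | 0.293 | 0.447 |

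With T0 completed before allocation or disclosure, this source of b is zero and the rate is 0.05. These figures show how sensitive the analysis is. They do not estimate what will happen.

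**The case against.** A reader might infer that the protocol has been shown to take baseline after patients know their arm. The documents do not support that. The order rests on a single sentence whose two parts are joined by a plain conjunction. The flow diagram, where the sequence would normally be drawn, is not available here. Table 1 puts the SCID, which certainly precedes allocation, in the same T0 column as the HRSD and PHQ-9, so part of T0 is early and other parts may be too. The time of disclosure is not stated, and without disclosure before T0 there is no bias. These points stand, and they turn the finding into one about unsafe wording.

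A reader might also treat the HRSD and the self-report scales as equally exposed. They are not. Raters are blinded, patients are asked not to reveal their arm, and an interviewer who learns it is replaced. This limits rater bias in the primary outcome, but it does not stop a patient from describing symptoms differently.

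A third inference is that disappointed control patients would skip T0 and so undermine the intention-to-treat set. That is conjecture. The plan includes everyone randomised, imputes missing values and tests whether the missing-data pattern interacts with treatment and change. This partly answers the worry, so it is not pressed here.

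Finally, outcomes that do not use change from baseline are unaffected. Remission, defined by an absolute PHQ-9 score, is one.

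**Conclusion.** The concern holds in a limited form. The only visible statement on sequence names allocation before the initial assessment, patients are unblinded, and nothing visible protects T0 from knowledge of the arm. A team that followed the text could therefore collect a post-randomisation baseline for outcomes analysed as change.

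The bias arises only if two things are true: patients learn their arm before completing T0, and their answers then shift differently by arm without the same shift persisting to follow-up. The documents establish neither, and they give no size or direction. The 31 to 42% figure depends on an assumed 1-point shift and an assumed SD of 6 to 8, and should not be read as expected bias. Exposure is greatest for the PHQ-9 and the other online questionnaires and smaller for the HRSD and QIDS-C. The text warrants correction because the remedy is nearly free and an altered baseline cannot be recovered later. If actual practice is already in the safe order, the sentence misdescribes it and still needs changing.

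**What to change.** In the section on eligibility and randomisation, state that all T0 measures (HRSD, QIDS-C and the online questionnaires) are completed before the independent researcher draws the allocation. If that is not feasible, state that they are completed before the allocation is disclosed to the patient. Label the T0 column of Table 1 in the same way, and check that Figure 1 shows the same order.

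The sample size stays at 200 and no measure is added. Observer ratings are already done by telephone, so the HRSD and QIDS-C could be given in the same contact as the SCID. The small downside of completing T0 before randomisation is that patients who do not finish T0 are not randomised, so somewhat more may need to be screened.

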**Figure 1 F1:**
[figure not shown]
Study flow diagram.

### Assessments

Self-report and observer-rated assessments will take place at baseline, post-intervention (three weeks after randomisation), at intake for inpatient treatment, weekly during inpatient therapy, and after completion of inpatient therapy (see Figure 1 and Table 1 for a detailed overview). Self-report data will be collected using a secure web-based assessment system (AES, 256-bit encrypted), and observer-based assessments will be conducted via the telephone by trained interviewers. Observer-rated assessments will be recorded to examine interrater reliability. In cases of disagreement, the two raters will discuss until a consensus is formed, and the rating agreed upon will be used for further analyses. If no agreement is reached after discussion, the assessment will be rated by an experienced diagnostic rater, and this rating will be used for analysis.

### Blinding

The research staff conducting the observer-based rating of depressive symptoms will be blinded to the participants’ assigned conditions. Considerable effort is being undertaken to ensure blindness, including the following: (a) an explanation to the participants as to why it is important not to inform the interviewer about the condition to which they were assigned, (b) a written reminder in the interview manual prompting the interviewer to ask the participant not to inform him or her about the randomisation status, (c) verbal reminders to the patient before the interview, and (d) a documentation after the assessment of whether or not the interviewer is still blind to the treatment condition. If the interviewer finds out about the treatment condition another independent interviewer will conduct the interview instead. Participants will not be blinded to the treatment condition.

### Interventions

#### GET.ON-Mood Enhancer-WL–experimental group

The primary purpose of the web-based intervention (GET.ON-Mood Enhancer-WL) is to reduce depressive symptomatology prior to intake for inpatient treatment. In addition GET.ON-Mood Enhancer-WL aims to prepare patients for subsequent inpatient therapy by providing relevant information (psycho education) and using effective and well known elements that are mainly based on behavioural therapy and problem-solving therapy. Abundant evidence exists to support components such as psycho education [18,35], behavioural activation [41,42], and problem solving [43,44] in the treatment of major depression.

A previous meta-regression analysis examining the relationship of treatment intensity to treatment outcome in the treatment of depression indicated that more frequent therapy sessions may be associated with a better outcome compared to less frequent sessions [45]. Thus, we included six modules and advised participants to complete at least one, but preferably two, lessons per week. In all, the training lasts approximately three weeks. We will not include more modules because (a) a recent meta-analysis [46] found web-based interventions for depression including more than seven modules to be less effective (*d* = 0.36) than interventions with seven or fewer modules (*d* = 0 .75) and (b) we wanted to lower the threshold for individuals as much as possible. Table 2 gives an overview of the sessions and their content.

**Table 2 T2:** Overview of content

**Session**	**Content**
Session 1: psychoeducation	First, patients should learn about their disease (symptoms, causes, and types of depression). In addition, the role of motivation in getting through this program should be emphasised.
Sessions 2 and 3: behavioural activation	Second, two behavioural activation sessions will teach the patient about the association between activity and mood. Thus, positive activities can be planned and implemented into the daily routine. In addition, possible obstacles will be considered. The planning of positive activities remains part of the program during the subsequent sessions. Furthermore, participants can work through the facultative module about sleep problems.
Sessions 4 and 5: problem-solving techniques	Sessions 4 and 5 are concerned with problem solving in which the patient learns to distinguish between solvable and unsolvable problems and practises using a six-step plan as a tool to solve problems. Information about unsolvable problems is given as well. Moreover, techniques to stop worrying are introduced.
Session 6: evaluation and preparation	Finally, the patient evaluates his gains and receives a summary of the program. Furthermore, he is encouraged to think about a future plan (such as choosing topics to work on during his inpatient stay).

Given the fact that some studies show a better effect for interventions with at least a low level of guidance compared to unguided interventions [46-48], this strategy might be a promising approach to encourage high treatment adherence. Therefore GET.ON-Mood Enhancer-WL provides a low level of guidance, including individualised feedback for the patient after finishing each of the six sessions. This feedback will be given by psychotherapists-in-training who will receive weekly supervision by an experienced clinician. After completion of the program, there will be no further guidance provided, but the patient will be free to continue with the program or to repeat the exercises.

Some studies have found that highly interactive interventions are more engaging, create higher expectations for improvement, and promote increased motivation and satisfaction in general [49,50]. Hence, the program contains several interactive components for the patients, including a diary to rate their mood and activity level, videos, testimonials, exercises, homework exercises, optional modules, and a library. A strong focus is placed on transfer tasks (homework assignments) to integrate newly acquired strategies and techniques into daily life. In the beginning of each subsequent lesson, participants are invited to reflect on their experiences with the newly acquired skills. The training is adaptive in a sense, as the content is tailored to the specific needs of the individual participant by continuously asking participants to respond by choosing from various response options. Subsequent content is then tailored to the participant’s response. Using responsive web design, participants can follow the program on the internet using a computer, tablet, or mobile phone. An integrated read-aloud function allows participants to follow an audio narration of the lessons.

#### Treatment as usual (TAU)–control group

TAU includes a wide variety of treatment alternatives, such as antidepressant medication, counselling, face-to-face psychotherapy, or no treatment at all. However, to control for potential confounding effects, treatment utilisation as well as changes in the dose of antidepressant medication will be closely monitored during the study period.

#### Inpatient treatment–both groups

Inpatient treatment will generally base on Cognitive Behavioral Therapy (CBT). Patients will receive one to two session of individual therapy (50 minutes) and an average of six sessions of group therapy (90 minutes) per week. Interventions will be supplemented with sports-and physiotherapy, as well as medical treatment (including medication) when necessary. Duration of treatment usually range between 21 and 56 days.

### Sample size

This study will be designed to detect a difference of *d* = 0.40 between the groups as the primary outcome. As patients expect to be treated for their depression in the subsequent inpatient psychotherapeutic treatment, we do expect a somewhat smaller effect size for our intervention than what has been found in the most recent meta-analysis of internet-based guided self-help treatments for depression [35]. With a power of 0.80 in a two-tailed test and *α* = .05, a sample of *n* = 200 participants would need to be included at baseline (calculated using GPower 3.1).

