This trial has also several limitations: As the trial will be conducted within the context of routine mental health care, the time span between the post-treatment assessment (conducted after the web-based treatment) and the beginning of inpatient therapy depends on both the capacities of the clinic and the eagerness of the patient and therefore will vary between patients. We will assess post-treatment data in both conditions at three weeks after randomisation to ensure a comparable time frame. Hence, patients will be at varying states within the online training when the post-treatment assessment takes place. Furthermore, we chose not to include a placebo/attention control condition because the TAU condition cannot be foreknown and is expected to be quite heterogeneous. Besides it is our aim is to study the effectiveness of GET.ON Mood Enhancer-WL in addition to and compared with usual care, as is standard in pragmatic trials [72]. However, due to the lack of such an active control condition, the mechanisms responsible for any possible effects will remain unclear. Last, we will include follow-up assessments only until the end of inpatient treatment. Therefore, we cannot draw conclusions about the effects on the long-term course of symptoms.

In the long term, it would be a desirable step to increasingly implement a new procedure such as this into the daily routine of inpatient as well as outpatient therapy. It would be good practice for the therapist to know in detail what steps the patient has taken previously and to be able to continue the previous gains. This knowledge would assist both the patient and the therapist, saving time and effort, and allowing them to concentrate on further issues and to intensify the treatment process.

Future research could make use of a homogenous control group, focus on various modifications of the program to identify active ingredients, compare different interventions that are likely to be effective as pre-inpatient treatments, evaluate web-based interventions for other disorders than depression or change the setting into the field of outpatient therapy.

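### The 200 patients to be included at baseline are the complete-data requirement, so the stated 80% power leaves no room for the missing post-treatment HRSD data the plan foresees

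*Protocol article*

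**What the plan says.** The Sample size section sets the target effect: "This study will be designed to detect a difference of *d* = 0.40 between the groups as the primary outcome". The error rates and the total follow in one sentence, "With a power of 0.80 in a two-tailed test" and "in a two-tailed test and *α* = .05, a sample of *n* = 200", and the total is tied to recruitment: these "participants would need to be included at baseline (calculated using GPower 3.1"). No attrition rate, inflation step or pre-post correlation is given.

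Other sections of the article foresee loss:

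- Assessment of eligibility and randomisation: "Patients will be informed that they can withdraw from the study at any time, without any consequences for their subsequent treatment".
- Statistical analyses: "Missing data will be handled using multiple imputations (MI"), with pattern-mixture analyses to examine whether missingness affects the result.

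The primary outcome is the HRSD-24, rated by telephone at baseline and once afterwards (T3 in Table 1). On timing, the Discussion says: "We will assess post-treatment data in both conditions at three weeks after randomisation to ensure a comparable time frame". The analysis is a mixed-model analysis of variance on all randomised patients. Statistical analyses also allows one-sided tests for directional hypotheses.

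**The concern.** A sample-size calculation for a t-test returns the number of patients who contribute an outcome. The article uses that number as the count at entry. The two agree only if every patient recruited has the T3 HRSD interview. Because that score is measured once after baseline, a missed interview removes the patient's whole post-treatment observation of the primary outcome.

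What is at stake is how the result is read. A null result from a trial described as having 80% power for d = 0.40 counts as fairly strong evidence against an effect of that size. If the real figure is nearer 70%, it deserves less weight.

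**Working it through.** **Inputs.** From Sample size: d = 0.40 (so SD = 1), two-sided alpha 0.05, power 0.80, N = 200 at baseline. Assumed: 1:1 allocation, because the article says only "They will be randomly allocated to treatment conditions and complete initial assessment". Also assumed: missing T3 rates of 5% to 30%, because none is given.

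**Step 1: reproduce the stated figure.** With n per arm, the noncentrality is d × √(n/2) on 2n − 2 degrees of freedom. Solving for power 0.80 at d = 0.40 gives n = 99.08, so 100 per arm and 200 in total. At n = 100 the noncentrality is 0.40 × √50 = 2.828, the critical value is 1.972 and power is 0.804. The stated 200 is reproduced exactly. A one-sided 0.05 test would need 78 per arm, 156 in total, so the calculation was indeed two-sided.

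**Step 2: is there a margin?** With 99 per arm, power is 0.7997. Losing one patient per arm uses it up.

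**Step 3: apply missing T3 data.** With n = 100 × (1 − missing rate) per arm and the same t-test:

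| Missing at T3 (assumed) | n per arm | Power at d = 0.40 | d detectable at 80% power |
|---|---|---|---|
| 0% | 100 | 0.804 | 0.40 |
| 5% | 95 | 0.783 | 0.41 |
| 10% | 90 | 0.761 | 0.42 |
| 20% | 80 | 0.710 | 0.45 |
| 30% | 70 | 0.652 | 0.48 |

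**Step 4: how far could the planned analysis change this?** The t-test is the basis of the stated figure but not the planned model. Two forms bracket the possibilities, with r the pre-post correlation (assumed) and d on the raw-score SD.

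- Change score (group by time): effective d = 0.40/√(2(1 − r)).
- Baseline-adjusted (ANCOVA): effective d = 0.40/√(1 − r²). For example, r = 0.5 gives 0.40/√0.75 = 0.462.

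Power at 20% missing (80 per arm):

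| r (assumed) | Change score | ANCOVA |
|---|---|---|
| 0.3 | 0.57 | 0.75 |
| 0.4 | 0.63 | 0.78 |
| 0.5 | 0.71 | 0.83 |
| 0.6 | 0.80 | 0.88 |
| 0.7 | 0.90 | 0.94 |

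A change-score analysis at r = 0.5 has the same power as the t-test, and below 0.5 it has less.

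**Step 5: what could imputation recover?** The PHQ-9 is collected online at T0 to T3, separately from the telephone interview. Suppose such data explain a share R² of the T3 HRSD variance and are available for everyone. The effective n per arm at 20% missing is then roughly 100/(1 + 0.25 × (1 − R²)), where 0.25 = 0.20/0.80. For R² = 0.25 this is 84.2, with power 0.73; for R² = 0.49 it is 88.7, with power 0.75. Recovery is partial: power lies above 0.71 but below 0.80.

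**Step 6: sidedness.** With a one-sided 0.05 test, power is 0.88 at 100 per arm and 0.81 at 80 per arm.

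**The case against.** The strongest reply has four parts.

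- **The calculation is correct, and the article condenses a fuller protocol in which a dropout assumption may stand.** This is fair, and the point does not rest on a missing inflation step. It rests on the article's own statement that a complete-data number is the number to include at baseline.
- **Losses may be small.** The endpoint comes three weeks after randomisation, in patients required to be motivated. Planning for missing data is routine and implies no particular rate. This stands as a limit on size: at 5% missing, power is 0.783, a loss of about two points.
- **The planned analysis is not a complete-case t-test.** This stands too. A reader might infer that the design cannot deliver 80% power at any realistic loss. The article does not support that: at 20% missing, a baseline-adjusted analysis with r = 0.5 has power 0.83, and imputation with PHQ-9 data could regain part of the loss. It does not vindicate the stated figure either, because a change-score analysis with r = 0.4 has only 0.63. The article names no correlation and claims no such gain.
- **The main hypothesis is directional, so the test could be one-sided.** One-sided power would be 0.81 at 20% missing. But the power is stated for a two-tailed test, so this does not rescue the claim. It shows instead that the two sections disagree on something the power depends on.

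**Conclusion.** The point holds as a fault in a sample-size assumption, not as an arithmetic error. The 200 is exactly what a two-sided t-test needs with complete T3 data, so 80% power for d = 0.40 is conditional on no loss, while the article treats it as a property of the number recruited.

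On the article's own calculation, the shortfall runs from about 2 points of power at 5% missing to about 15 at 30% (0.804 to 0.652). This rests on 1:1 allocation and on attrition rates that are assumed. Whether the real power is above or below 0.80 cannot be settled from the article, since it depends on the unstated pre-post correlation, the imputation model and the sidedness of the test. Confidence is therefore moderate. The stated power should be corrected, but the point does not invalidate the design.

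**What to change.** No additional enrolment is needed. Either of two changes will do:

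1. **Restate the figure.** Say that 200 randomised patients give 80% power for d = 0.40 only with complete T3 HRSD data, and give power and detectable effect at an expected T3 completion rate. At an assumed 80% completion these would be about 0.71 and d = 0.45, before any gain from imputation.
2. **Justify 200 on a baseline-adjusted primary analysis.** Specify an ANCOVA-type model for T3 HRSD with baseline HRSD as covariate, and state the correlation and dropout used. At an assumed 20% missing, a correlation of 0.5 gives power 0.83, whereas 0.3 gives 0.75, so the choice of correlation needs support.

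In either case, state whether the primary test is two-sided or one-sided, so that Sample size and Statistical analyses agree.

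The first change costs only wording, and a somewhat less favourable power statement. The second also requires the form of the primary model to be fixed, which may recover the 80%.
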